### Outcomes

#### Primary outcome

The primary outcome is the rate of normal hips, defined as an acetabular index lower than 25 degrees on an antero-posterior radiograph, at the age of 12 months.

#### Secondary outcomes

The rate of normal hips, defined as acetabular index lower than 25 degrees on an antero-posterior radiograph, at the age of 24 months will be studied. Also, the relation between baseline patient characteristics and the rate of normal hips will be explored. Included patient characteristics are gender, birthweight, initial alpha angle, initial beta angle, laterality (right or left, unilateral or bilateral), history of DDH in relatives, breech presentation, swaddling, twin birth, parents/caregivers’ education level, ethnicity, range of abduction in flexion (degrees), and whether the child is the firstborn child of the parents/caregivers. Accordingly, the time to hip normalization is studied. Complications during the follow-up period will be examined. The compliance of wearing the abduction device in the abduction treatment group will be assessed using visual inspection of the abduction device and a parent/caregiver-question on the number of hours that the abduction device has been worn in the last 24 hours. Furthermore, resource use and costs will be assessed using standardized cost-questionnaires. The health-related quality of life (HRQoL) of the infant will be measured with the Visual Analogue Scale (EQ-VAS) of the youth version of the EQ-5D (EQ-5D-Y) and the Infant and Toddler Quality of Life Questionnaire Short Form (ITQOL-SF47), filled out by one parent/caregiver. Last, the HRQoL of one parent/caregiver will be measured with the EQ-5D-5L and parent/caregiver satisfaction with the treatment process will be assessed with the Visual Analogue Scale.

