## Background

Developmental Dysplasia of the Hip (DDH) is one of the most common pediatric orthopedic disorders, affecting 1–3% of all newborns [1]. DDH encompasses a wide spectrum of growth disorders of neonatal and infant hips, ranging from mild acetabular dysplasia with a well-centered femoral head to severe acetabular dysplasia with dislocation of the femoral head [1, 2]. Untreated DDH can lead to chronic pain, gait abnormalities, and early-onset hip osteoarthritis [1–3]. It is estimated that up to 26% of hip arthroplasties in patients aged 40 years or younger are performed due to untreated or insufficiently treated hip dysplasia [4].

Centered DDH refers to centered hips with acetabular dysplasia, classified as Graf type IIa-/IIb/IIc with ultrasound evaluation (Table 1) [3, 5]. The optimal treatment of centered DDH is currently under debate. Abduction treatment is the most used treatment method for children under six months of age with centered DDH worldwide [6]. However, it is approximated that 85% of immature dysplastic hips will normalize at the age of three months without treatment [7]. Also, it is estimated that more than 80% of centered DDH hips (Graf IIa- to IIc) under six months will normalize without treatment [8]. This suggests that ultrasonography screening at a young age might introduce DDH overdiagnosis and possibly unnecessary treatment of immature hips that are not truly pathological.

**Table 1 Tab1:** Ultrasonography classification of hip dysplasia by Graf [9]

Type	Alpha angle	Beta angle	Description
Ia	≥ 60	≤ 55	Normal, mature hip
Ib	≥ 60	> 55	Normal, mature hip
IIa +	50–59	> 55	Physiological immaturity, age appropriate (< 3 months old)
**IIa-**	**50–59**	** > 55**	**Maturational deficit (< 3 months old)**
**IIb**	**50–59**	** > 55**	**Delayed ossification (> 3 months old)**
**IIc**	**43–49**	** < 77**	**Critical zone**
D	43–49	> 77	Decentered
III	< 43		Decentered; perichondrium upward
IV	< 43		Decentered; perichondrium horizontal or downward

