### Eligibility criteria

The TReatment with Active Monitoring (TRAM)-Trial consists of infants aged 10–16 weeks who are diagnosed with centered DDH (Graf IIa-/IIb/IIc) with ultrasound evaluation. In case of bilateral DDH, only the hip with the most severe Graf classification at baseline will be included in the analyses. Additional inclusion criteria are good comprehension of the Dutch language and the written informed consent of the parents/caregivers. Exclusion criteria are hip instability (Graf type D/III/IV DDH), age < 10 weeks or > 16 weeks, (suspicion of) syndromic disease (e.g. arthrogryposis, cerebral palsy, Down syndrome), and prematurity (defined as a gestational age < 37 weeks).

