**Table 3 Tab3:**
[figure not shown]
Study procedures and questionnaires at follow-up time points of the TRAM-Trial

^1^ Patient characteristics: gender, birthweight, laterality (right/left, unilateral/bilateral), history of DDH in relatives, breech presentation, swaddling, twin birth, socio-economic status parents/caregivers, ethnicity, firstborn, age of parents/caregivers.

^2^ Extra compared to care-as-usual.

^3^ + 36 weeks measurements are only performed if the infant was 10 weeks of age at inclusion.

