### Statistical methods

Statistical analyses will be performed according to the intention-to-treat principle and per-protocol approach. The difference in rate of normal hips between active monitoring and abduction treatment at the age of 12 and 24 months will be analyzed with chi-square tests. The non-inferiority margin will be set to 10% and non-inferiority will be demonstrated if one side of the 95% confidence interval lies outside the non-inferiority margin.

A Kaplan Meyer analysis will be performed to study the time to hip normalization, with events defined as Graf I or acetabular index lower than 25 degrees at 12 months or acetabular index lower than 25 degrees at 24 months. Differences in survival curves will be studied and tested for statistical significance with the Log Rank test. The relation between patient characteristics and the rate of normal hips at the age of 12 and 24 months will be studied with prediction models. Using backward elimination, a multivariable cox regression model will be constructed. The Receiver Operating Characteristic (ROC) curve and Area Under the Curve (AUC) will be used as performance parameters, goodness-of-fit will be determined by inspection and publication of the calibration plot and publication of discrimination parameters, and internal validation of the model will be performed with bootstrapping. Compliance will be presented using descriptive analysis. The difference in the number of complications will be studied with a t-test (total number of complications) and chi-square test (number of infants with a complication). Differences in quality of life and parent/caregiver satisfaction will be determined with generalized estimated equations (GEE). The statistical analyses will be performed with SPSS version 25 (IBM SPSS Statistics for Windows; Armonk, New York: IBM Corp.).

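### The predictor list for normal hips includes the alpha and beta angles but neither infant age at the scan nor Graf type, so the model cannot tell IIa- from IIb at the same angles

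*Protocol article*

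**What the plan says.** The Secondary outcomes section names the candidate predictors: "Included patient characteristics are gender, birthweight, initial alpha angle, initial beta angle, laterality (right or left, unilateral or bilateral), history of DDH in relatives". The list continues with "breech presentation, swaddling, twin birth, parents/caregivers’ education level, ethnicity, range of abduction in flexion (degrees), and whether the child is the firstborn child". It carries no wording to mark it as a set of examples.

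The Statistical methods section gives the use: "The relation between patient characteristics and the rate of normal hips at the age of 12 and 24 months will be studied with prediction models". It then gives the method: "Using backward elimination, a multivariable cox regression model will be constructed". It names neither an age term nor a treatment term.

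Table 1 in the Background describes type IIa- as "Maturational deficit (< 3 months old") and type IIb as "Delayed ossification (> 3 months old"). Both rows show alpha 50–59 and beta above 55. The Eligibility criteria admit "infants aged 10–16 weeks who are diagnosed with centered DDH (Graf IIa-/IIb/IIc) with ultrasound evaluation". Allocation and blinding makes Graf type, with center, a stratification factor.

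**The concern.** The aim of this secondary outcome is to learn which infants end with a normal hip. The alpha angle is the natural leading predictor, but under the classification that the protocol adopts, an angle of 50–59 is a maturational deficit in a younger infant and delayed ossification in an older one. If age is not offered to the model, the same reading at 10 weeks and at 16 weeks is treated as the same finding. Backward elimination only removes candidates, so it cannot bring in one that was never listed.

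At stake is the usefulness of the prediction model. Any prognostic difference between IIa- and IIb, a distinction important enough to stratify on, would be averaged away or carried in part by whichever listed item happens to correlate with age.

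**Working it through.** The plan gives no figure to reproduce here. The check is a comparison of sections, followed by the cost of the change.

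**1. Can the listed items recover Graf type?**

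| Type | Alpha | Beta | Age in Table 1 |
|---|---|---|---|
| IIa- | 50–59 | > 55 | under 3 months |
| IIb | 50–59 | > 55 | over 3 months |
| IIc | 43–49 | < 77 | none given |

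Alpha separates IIc from the other two. Neither angle separates IIa- from IIb, because their ranges are identical. None of the other listed items records the infant's age. The listed set can therefore identify IIc, but not which of the other two types an infant has.

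**2. Does the trial enrol on both sides of the boundary?**

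Three months = 365.25 / 4 / 7 = 13.04 weeks, and entry runs from 10 to 16 weeks, so it does. If entry ages were evenly spread (an assumption, for illustration only), the share below the boundary would be (13.04 − 10) / 6 = 0.51 and the share above 0.49. Screening ultrasound is planned at three months, so the real split may differ. The conclusion needs only that both types are enrolled, and stratifying on both shows that the protocol expects this.

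**3. Are the missing items available?**

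Age is needed to apply the entry criterion, and Graf type is needed to randomize. Footnote 3 to Table 3 also makes one visit depend on the infant's age at inclusion. Footnote 1 lists "socio-economic status parents/caregivers, ethnicity, firstborn, age of parents/caregivers" and not the infant's age. The body of that table is not visible in the text reviewed, so this is no evidence that infant age goes unrecorded.

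**4. What does the change cost?**

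- Evaluable infants: 800 × (1 − 0.10) = 720.
- Non-normal hips at the assumed 80% rate: 720 × 0.20 = 144.
- Listed parameters: 14, taking one each and two for laterality (side; unilateral or bilateral).

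| Model | Parameters | Non-normal hips per parameter |
|---|---|---|
| As listed | 14 | 144 / 14 = 10.3 |
| + age | 15 | 144 / 15 = 9.6 |
| + age and arm | 16 | 144 / 16 = 9.0 |
| + Graf type (two terms) and arm | 17 | 144 / 17 = 8.5 |

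If education and ethnicity take several categories (20 parameters assumed), adding age and arm moves the ratio from 144 / 20 = 7.2 to 144 / 22 = 6.5. These ratios use the smaller outcome class, which suits normal versus not normal at a fixed age. In a Cox model of time to normalization the events are the normalizations, so the count would be larger and the cost smaller.

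**The case against.** The strongest reply is that the list may not be closed. The relation is to be explored, nothing says that only these items may be used, and the article's two lists already differ: the Table 3 footnote has parental age, and socio-economic status where the Secondary outcomes section has education level. A full analysis plan may add age. That is fair as to intent. But the list is an enumeration without qualification, and a plan that follows it inherits the gap. Naming the candidates is a choice stated in this document, not a detail left for later.

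It is also fair that the entry band is only six weeks, that IIc has no age split in Table 1, and that no figure in the protocol shows how much prediction would suffer. These points limit the importance, not the fact.

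Some stronger readings are tempting but unsupported:

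- **That allocated arm is left out of the model.** Arm is not a baseline patient characteristic, so its absence from this list proves nothing. The Statistical methods section neither includes nor excludes it.
- **That omitting arm would confound the predictors.** Allocation is randomized, so arm is independent of baseline characteristics in expectation.
- **That the 70% and 80% rates in the sample size section measure what a missing arm term would cost.** The 10-point gap is the non-inferiority margin. The trial's hypothesis is that monitoring is not lower.
- **That entry age alone sets the time to the 12-month radiograph at 36 to 42 weeks** (52 − 16 and 52 − 10). The radiograph has a window of ± 1 month, itself wider than the entry range, and all infants are read at about the same age.
- **That an alpha-by-age interaction is required.** It is a reasonable modelling preference, but nothing in the document makes its absence an error.

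**Conclusion.** The point holds for infant age and Graf type. Followed as written, the prediction model has no means of distinguishing IIa- from IIb at the same angles, although Table 1 separates them by age alone, enrolment spans the boundary, and randomization is stratified on the type.

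This rests on reading the list as the full candidate set and on taking Table 1 as the classification in use. The resulting loss of discrimination or calibration cannot be sized from the document. The analysis is secondary and exploratory; the primary outcome, the margin and the sample size are unaffected. On allocated arm, the document is only silent, which justifies a clarification and nothing more.

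**What to change.** In the Secondary outcomes section, add infant age at the baseline ultrasound, as a continuous variable, to the characteristics. Take it on the date of the scan that supplies the alpha and beta angles. Graf type may be added or used instead, but it keeps only the split at three months, whereas continuous age keeps the whole range. In the Statistical methods section, state that this term stays in the model regardless of backward elimination.

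As a secondary clarification in the same place, state that allocated arm is kept as a model term, so that predictions can be given under each strategy. A main effect for arm assumes that the predictors act alike in both arms. Separate models by arm would relax this at a much higher price: about 144 / 2 = 72 non-normal hips each, or 72 / 15 = 4.8 per parameter with 15 parameters.

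The recommended change needs wording only. Entry age, Graf type and arm are already known for every infant, so no new data are needed. The downside is one to three extra parameters in an exploratory model.

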### Participant timeline

A participant timeline of measurement moments of the TRAM-Trial is shown in Table 3.

**Table 3 Tab3:**
[figure not shown]
Study procedures and questionnaires at follow-up time points of the TRAM-Trial

^1^ Patient characteristics: gender, birthweight, laterality (right/left, unilateral/bilateral), history of DDH in relatives, breech presentation, swaddling, twin birth, socio-economic status parents/caregivers, ethnicity, firstborn, age of parents/caregivers.

^2^ Extra compared to care-as-usual.

^3^ + 36 weeks measurements are only performed if the infant was 10 weeks of age at inclusion.

### Sample size and recruitment

We hypothesize that the rate of normal hips of infants treated with active monitoring is not lower than the rate of normal hips of infants treated with an abduction device. Based on the study results of Ömeroglu et al. [18], we assume a rate of normal hips of 80%. The inferiority margin was set to 10%, based on consensus in the study group (70% adequate treatment in the active monitoring group, 80% adequate treatment in the abduction treatment group). With an alpha of 0.05 and power of 90%, the sample size is 370 infants per group. Accounting for 10% lost to follow up, a total of 800 infants (400 per group) is warranted.

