## Methods/design

### Trial design and study setting

This is a multicenter, parallel-group, open-label, non-inferiority randomized controlled trial studying the (cost-)effectiveness of active monitoring versus abduction treatment for infants with centered DDH in fourteen hospitals in the Netherlands (Amphia Hospital, Amsterdam University Medical Center, Erasmus Medical Center, HagaZiekenhuis, Leiden University Medical Center, Maastricht University Medical Center, Máxima Medical Center, Medisch Spectrum Twente, Noordwest Ziekenhuisgroep, Onze Lieve Vrouwe Gasthuis, Reinier Haga Orthopedic Center, Sint Maartenskliniek, Spaarne Gasthuis, and University Medical Center Groningen). As part of the Dutch national DDH screening program, youth healthcare professionals will refer at-risk infants for an ultrasound evaluation at the age of three months (or sooner in case of suspected dislocation) [17]. Infants will be identified and recruited after diagnosis at outpatient clinics of the participating orthopedic departments. After diagnosis and assessment of the eligibility criteria, parents/caregivers will receive the written patient information leaflet. Parents/caregivers will return for a standard-care consultation to sign the informed consent after a reflection period of seven days. After written informed consent has been obtained, randomization and baseline measurements will be performed. Infants will be followed up until the age of 24 months.

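### The sample-size figures do not fit together: 400 per group less 10% loss leaves 360 evaluable infants, not the stated 370

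*Protocol article*

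**What the plan says.** The Sample size and recruitment section of the protocol article assumes 80% normal hips. On the margin it says "The inferiority margin was set to 10%, based on consensus in the study group", followed by a bracket: "70% adequate treatment in the active monitoring group, 80% adequate treatment in the abduction treatment group". The size comes next: "With an alpha of 0.05 and power of 90%, the sample size is 370 infants per group". The allowance for loss follows directly: "Accounting for 10% lost to follow up, a total of 800 infants (400 per group) is warranted". The section does not say whether alpha is one- or two-sided, and it names no formula.

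Trial design and study setting describes a "multicenter, parallel-group, open-label, non-inferiority randomized controlled trial". Statistical methods repeats the 10% margin and judges it with a 95% confidence interval.

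**The concern.** Three figures printed side by side (370 required, 10% loss, 400 enrolled) should be linked by one division, and they are not. This can be checked from the paragraph alone. It does not depend on the choice of formula or on anything that a fuller protocol or a statistical analysis plan might add.

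The paragraph is where the trial justifies randomising 800 infants. Anyone judging how much loss is tolerable, or whether recruitment may close at 800, would take from it that 10% loss still leaves the 370 tied to 90% power. It does not.

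**Working it through.** **Inputs (Sample size and recruitment, unless noted).** 80% normal hips; margin 10 percentage points; rates of 70% and 80% given with the margin; alpha 0.05, sidedness not stated; power 90%; 370 per group required; 10% loss; 400 per group enrolled. Assumption: the 95% interval in Statistical methods is two-sided, so the non-inferiority decision is made at one-sided 0.025. Hence z = 1.960 for alpha and 1.2816 for power.

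**Step 1: the loss allowance.**
- Evaluable from the stated enrolment: 400 × 0.90 = 360, which is 10 per group (20 in total) below the requirement. That is 10/370 = 2.7%.
- Enrolment needed to keep 370: 370/0.90 = 411.1, so 412 per group and 824 in total.
- The cruder convention, 370 × 1.10, gives 407.
- Loss that 400 can absorb while keeping 370: 1 − 370/400 = 7.5%.

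Neither way of adding 10% turns 370 into 400.

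**Step 2: can 370 be reproduced?** With 80% in both groups, the variance term under the alternative is 0.8×0.2 + 0.8×0.2 = 0.32. With 70% and 80% at the margin, the null variance term is 0.7×0.3 + 0.8×0.2 = 0.37. Pooled at 75%, it is 2×0.75×0.25 = 0.375.

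- Null variance at 70%/80%: n = [1.960√0.37 + 1.2816√0.32]² / 0.10² = 367.5, so **368**.
- Null variance pooled at 75%: n = [1.960√0.375 + 1.2816√0.32]² / 0.10² = 370.6, so **371**.
- Usual unpooled formula: n = (1.960 + 1.2816)² × 0.32 / 0.10² = 336.2, so **337**. At one-sided 0.05 it gives 275.
- Score-based (Farrington-Manning), one-sided 0.025: 340, or 360 with continuity correction.

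The first two use only rates printed in the paragraph and come within 1% of 370.

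**Step 3: power at 360 and at 370 per group (true rates 80%/80%, one-sided 0.025).**

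| Formula | Required n | Power at 370 | Power at 360 |
|---|---|---|---|
| Null variance at 70%/80% | 368 | 90.2% | 89.4% |
| Null variance pooled at 75% | 371 | 89.9% | 89.1% |
| Unpooled | 337 | 92.5% | 91.8% |

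Rows 1 and 2 use Φ[(0.10√n − 1.960√V₀)/√0.32], where V₀ is 0.37 or 0.375. Pooled, at n = 360: (1.8974 − 1.2002)/0.5657 = 1.232, and Φ(1.232) = 0.891. Row 3 uses Φ[0.10/√(0.32/n) − 1.960]. An exact binomial calculation for a Wald 95% interval gives 91.9% at 360.

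**Step 4: do all four statements hold under any formula checked?** Under the formulas that reproduce 370, the 360 remaining after 10% loss gives slightly less than 90% power. Under the unpooled formula, 360 is more than enough, but the required size is then 337. The continuity-corrected score formula needs 360, which 400 delivers exactly, but then the requirement is not 370 either. So 370 required, 10% loss, 400 enrolled and 90% power never hold together.

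**The case against.** The strongest defence is that the mismatch is rounding. The gap is 2.7% of 370, and 412 against 400 is 12/400 = 3.0%. Under the formula at 70%/80% that reproduces 370, the cost is less than one percentage point of power (90.2% to 89.4%). Under the commonest formula, power stays above 90%. A condensed article also commonly leaves the formula and software to the full protocol. This defence settles the size of the problem, and the missing formula is not in itself a fault. It does not remove the error: the rounding goes below the stated requirement and turns a stated 10% allowance into 7.5%.

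A reader might infer several stronger points that the document does not support:

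- *That 370 cannot be obtained from the stated inputs, or that 337 is the true requirement.* Step 2 gives 368 and 371 from the printed rates; 337 is the result of one convention among several.
- *That loss was counted twice, because 336.2 × 1.10 = 369.9.* Nothing says that 370 already includes loss, and a second multiplication by 1.10 gives 407, not 400. The match is a coincidence as far as the text shows.
- *That 70% is the expected rate under active monitoring.* The bracket directly follows the margin and reads naturally as its boundary. The same paragraph assumes a single rate of 80% and hypothesises that active monitoring is not lower.
- *That the trial was sized as a two-sided difference test of 80% against 70%.* That would need 389 to 392 per group, and 360 would give 87.4% power, but the stated non-inferiority design does not fit this reading.

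**Conclusion.** The point holds as an inconsistency among stated figures. Enrolling 400 per group with 10% loss delivers 360 evaluable infants per group, not 370; delivering 370 would take 412 per group (824 in total). The loss step is certain because it rests only on printed numbers.

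The consequence for power is small: about 89% to 92% at 360 per group, depending on the formula. This assumes 80% normal hips in both groups, a 10-point margin and one-sided 0.025. The figure of 370 is untraced in the text but not shown to be wrong. This is a minor correction and not evidence of a seriously underpowered trial.

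**What to change.** Keep 800 and restate the paragraph. Name the formula and one-sided 0.025 (two-sided 95% interval), and say that 400 per group leaves 360 after 10% loss, or alternatively that 370 corresponds to 7.5% loss. Then give the power at 360 under the named formula:

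- If the null-variance formula was used, keep about 370 as the required size and state about 89% power at 360.
- If the unpooled formula is adopted, replace 370 with 337 as the required size and state about 92% power at 360.

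The sponsor should choose according to how 370 was actually derived. Optionally, add a clause saying that 80% is assumed in both groups and that 70% is the margin boundary.

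The cost is the rewording of one paragraph, with no additional infants and no change to the design.
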